## Abstract

**Background:**

The prevalence of smoking among cervical cancer survivors is high and evidence-based smoking cessation interventions are critically needed. This paper describes the study design, methods, and data analysis plans for a randomized clinical trial (RCT) designed to evaluate the efficacy of a novel, personally tailored SMS-delivered text-based digital treatment adjuvant designed to enhance the long-term efficacy of a “**M**otivation **A**nd **P**roblem-**S**olving” (**MAPS**) approach for smoking cessation among individuals with a history of cervical intraepithelial neoplasia (CIN) or cervical cancer. MAPS is a phone counseling approach designed to facilitate long-term abstinence that comprises 6 counseling calls over 12 months. The current trial is evaluating the efficacy of **MAPS+**, which comprises all MAPS components plus a 24-month digital treatment adjuvant. This trial represents a logical extension of our previous RCT, which compared the efficacy of MAPS to a quitline control condition and found that MAPS resulted in greater than a 2-fold increase in smoking abstinence at 12 months (i.e., 26.4% vs. 11.9%). This treatment effect was no longer significant at 18 months, suggesting that efficacy dissipated as time from the end of treatment increased. The primary aim of the current trial is to compare the efficacy of MAPS + and ST in facilitating long-term abstinence.

**Methods:**

Individuals who smoke and have a history of cervical cancer or CIN (N = 340) are recruited throughout Florida and randomly assigned to **Standard Treatment** [**ST**] or **MAPS+**. ST participants are electronically connected with the Florida Quitline. MAPS + consists of 6 proactive MAPS-based counseling calls over 12 months plus the novel, personally tailored, text message-based treatment adjuvant delivered over 24 months. All participants receive 12 weeks of combination nicotine replacement therapy (patch and lozenge) and are followed for 24 months. Participant recruitment commenced in December 2022 and is ongoing.

**Discussion:**

This study builds on promising results from our recent trial which found that MAPS was associated with substantially higher abstinence from smoking at the end of the 12-month treatment period. Finding that this low-burden, personally tailored digital treatment adjuvant improves the long-term efficacy of MAPS would have important clinical and public health implications.

**Trial registration:**

Clinical Trials Registry NCT05645146; https://clinicaltrials.gov/ct2/show/NCT05645146; Registered on December 9, 2022.

## Background

In the presence of HPV, smoking is a primary risk factor for cervical intraepithelial neoplasia (CIN) – the immediate precursor to cervical cancer – and cervical cancer [1–5]. Continuing to smoke after a cancer diagnosis is associated with poor treatment response, increased risk of recurrence, second primary cancers and other diseases [3, 6–10]. In the US, there are estimated to be nearly 300,000 cervical cancer survivors [11]. Furthermore, approximately 200,000 individuals are diagnosed with CIN each year, [12] which places them at substantially elevated risk of developing cervical cancer. An alarming one-third of cervical cancer survivors report current smoking, a prevalence that is higher than among any other subgroup of cancer survivors [13]. Smoking cessation among individuals with a history of CIN or cervical cancer is a critically important clinical and public health issue. With few exceptions, [14, 15] smoking cessation interventions for the general population of cancer survivors have failed to demonstrate efficacy [13, 16]. Thus, there is a pressing need for efficacious, cost-effective, and sustainable interventions with broad dissemination potential for survivors of CIN and cervical cancer. The current study was designed to help fill this need.

Other than our previous trial, [15] no tobacco cessation studies that we know of have specifically targeted individuals with a history of CIN or cervical cancer, even though these populations have unique characteristics which warrant a targeted approach. Multiple studies have documented that cervical cancer survivors suffer moderate to poor health-related quality of life [17] and longstanding psychosocial sequelae including anxiety, depression, stress, relationship issues, and difficulty with sexual functioning [17–21]. Furthermore, cervical cancer survivors with lower SES and limited social support are at even greater risk for poor outcomes [17, 22, 23]. Because our Motivation And Problem Solving+ (MAPS+) approach is built around a Wellness Program that addresses life events, stressors, and other concerns (e.g., anxiety, stress, fear of cancer or cancer recurrence, family conflicts and relationship issues), it is especially well-suited to addressing concerns of particular relevance to survivors of CIN or cervical cancer.

## MAPS + overview and rationale

MAPS is a holistic, dynamic framework for behavior change that integrates treatment elements from both motivational interviewing [24, 25] and social cognitive theory [26–28]. It is designed for all individuals regardless of their readiness to quit, and specifically targets motivation, agency/self-efficacy, and stress/negative affect. Counselors are trained to carefully assess and respond to changes in motivation so that treatment strategies are appropriately matched in the moment. MAPS is built around a Wellness Program that, in addition to focusing on smoking, addresses life events, stressors, and other immediate concerns. By addressing the larger context in which smoking cessation occurs, not only are many of the barriers to successfully quitting smoking addressed, but treatment engagement is also likely to be enhanced because individuals perceive that the counselors care about them as whole people and are not solely interested in their smoking behavior.

Our team recently completed a trial that evaluated the efficacy of MAPS among individuals with a history of CIN or cervical cancer and results indicated that MAPS was associated with a greater than two-fold increase in smoking abstinence at 12 months compared to a quitline treatment control condition. Unfortunately, the large treatment effect observed at 12 months diminished over time and was no longer significant at 18 months [15]. The personally tailored text-based digital treatment adjuvant being evaluated in the current study is intended to enhance long-term abstinence through extending support and reinforcing motivational enhancement and coping skills training provided by the MAPS counselors. Text message content was designed to emphasize and reinforce specific MAPS-based treatment content areas such as managing cravings, practicing coping skills, handling ambivalence about quitting smoking and maintaining abstinence, stress management, relationship issues, and survivorship-specific concerns. Furthermore, this treatment content is tailored to participants’ need for support in specific areas, their smoking status, and their self-reported levels of motivation, agency and stress/negative affect. The purpose of the 24-month digital treatment adjuvant is to extend and enhance participants’ relationships with their MAPS counselors. This is achieved by training counselors to encourage participants to utilize the support and information provided by the text messages between counseling calls and after counseling has ended. Counselors are also trained to refer participants back to specific text content for acute challenges such as managing cravings, anticipating and planning for “high risk” situations and refreshing coping skills.

This paper describes the research design, methods, and data analysis plans for an ongoing randomized clinical trial (RCT) designed to evaluate the efficacy of MAPS + in facilitating smoking cessation among survivors of CIN or cervical cancer. The primary aim of the trial is to compare the efficacy of MAPS + in facilitating smoking cessation with standard treatment (ST). A secondary aim is to evaluate motivation for smoking cessation, agency, and stress/negative affect as prospective mediators of the difference in abstinence between the MAPS + and ST treatment groups. Whereas each is a likely mechanism for both interventions, the relative importance may differ. For example, higher levels of quit motivation may mediate abstinence in ST, whereas higher levels of agency may mediate abstinence in MAPS+.

## Methods and design

### Study design overview

A 2-group RCT is underway to compare the efficacy of MAPS + vs. ST (Fig. 1).

**Fig. 1 Fig1:**
[figure not shown]
Study flow

ST participants are electronically connected with Tobacco Free Florida (i.e., the Florida Quitline). MAPS + consists of 6 proactive MAPS-based phone counseling sessions over 12 months plus a novel digital treatment adjuvant, which is delivered over 24 months. All participants receive 12 weeks of combination nicotine replacement therapy (patches + lozenges). Assessments are completed at baseline, 3, 6, 12, 18 and 24 months following baseline. All assessments are completed remotely (over the phone or via a secure REDCap link). In addition, brief REDCap-based smartphone assessments are delivered every 30 days, which are used to drive the personalized text-based treatment content in the MAPS + condition, are administered throughout the 24-month treatment period. These assessments are also delivered to ST participants to ensure that both treatment conditions are matched on assessment burden. The primary outcome is self-reported 7-day point prevalence abstinence over time throughout the 24-month assessment period [29, 30]. Secondary outcomes include additional smoking-related outcomes (i.e., biochemically verified abstinence, length of abstinence, continuous abstinence, cigarettes per day, quit attempts).

It is hypothesized that self-reported, 7-day point prevalence abstinence rates will be greater in MAPS + than in ST over time throughout the 24-month assessment period. For secondary outcomes, it is hypothesized that MAPS+ (vs. ST) participants will have higher biochemically confirmed abstinence rates at 24 months and across all assessments, make more quit attempts, report longer periods of abstinence, and report smoking fewer cigarettes per day across all assessments throughout the 24-month study period.

### Recruitment and participants

Participant recruitment began in December 2022. Participants (target sample size = 340) are recruited through internet advertisements (i.e., Facebook, Instagram, Google pay-per-click ads, Craigslist) and internet-based, healthcare provider or community referrals (e.g., ClinicalTrials.gov, flyers, word-of-mouth). Inclusion criteria are: (1) ≥ 18 years of age; (2) ≥ 100 lifetime cigarettes; (3) English-speaking; (4) self-report of smoking ≥ 1 cigarette in past 30 days; (5) history of cervical cancer or CIN; (6) working smartphone; (7) valid home address; and (8) reside in Florida at the time of study enrollment. Exclusion criteria are: (1) medical condition precluding NRT; (2) currently receiving behavioral or pharmacological tobacco treatment; (3) household member enrolled in the study.

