### Procedures

This study was reviewed and approved by Advarra, the H. Lee Moffitt Cancer Center institutional review board (IRB) and is registered on ClinicalTrials.gov (NCT05645146). After completion of a brief online pre-screener, potential participants are contacted by research staff via phone to complete a more detailed screening. All eligible individuals are invited to participate. A detailed description of the study is provided, and verbal informed consent is obtained. Individuals who decline or are ineligible are referred to other cessation programs. Individuals who meet all eligibility criteria and consent to participating in the study complete the baseline assessment either over the phone with a research coordinator or via a secure electronic REDCap link sent via text message or email based on their preference. Following completion of the baseline assessment, participants are randomized to MAPS + or ST using a 1:1 ratio with a block size of 4 following stratification on the following variables: daily vs. nondaily smoking; CIN and early cancer stages (Stages I and Stage II) vs. advanced cancer stages (Stage III and Stage IV), and pending or in active treatment vs. completed treatment. The randomization sequences were created by the study statistician and implemented in REDCap.

Assessments occur at baseline, 3, 6, 12, 18 and 24 months and take approximately 20 min to complete (see Table 1). Participants are given the option to complete the assessments via phone or via a hyperlink as a REDCap-administered self-assessment. Compensation is provided after each assessment is completed (6 assessments x $30 = $180). Participants who report abstinence at any follow-up point are mailed a cotinine test. Compensation for returning cotinine tests is $30 per assessment.

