**SMOKING ABSTINENCE**			
Smoking Status (SRNT)	X	X	X

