#### Smoking abstinence

*Self-report smoking abstinence* assessments are based on recommendations from the Society for Research on Nicotine and Tobacco (SRNT) [30] and include abstinence assessments at all follow-up assessments. We are evaluating two point-prevalence abstinence measures: (1) no smoking during the previous 7 days, and (2) no smoking during the previous 30 days. Point-prevalence abstinence rates (intent-to-treat) will be estimated using generalized estimating equations.

*Biochemically verified abstinence.* Biochemically verified abstinence is assessed using saliva cotinine [29]. Participants who report 7-day point-prevalence abstinence at any follow-up assessment are mailed a prepaid envelope, instructions for providing a saliva sample, and a saliva collection kit. Research staff are available to speak with participants by phone and/or email should the participant have questions about the collection process. The participant is asked to return the sample via mail using a pre-paid envelope and, upon receipt of returned saliva samples, participants are compensated $30.

*Smartphone assessments*. All participants are asked to complete brief monthly assessments through REDCap (sent via SMS) for 24 months. For participants randomized to MAPS+, these 5-item monthly assessments are used to check in and offer personally tailored treatment content delivered via text messages and matched on both (1) areas in which participants indicate a need for support, and (2) smoking status, perceived stress, motivation, and self-efficacy. Participants randomized to ST also receive monthly assessments of smoking status, perceived stress, motivation, and self-efficacy (four items) to ensure that both treatment conditions are matched on assessment contacts. However, ST participants do not receive additional treatment after completing these monthly assessments.

*Primary and secondary outcomes*. Our primary outcome is self-reported 7-day point prevalence abstinence at 24 months where participants who report no smoking in the previous 7 days are considered abstinent. This follows recommendations for community-based smoking cessation trials that do not involve in-person assessments [29, 30]. Secondary outcomes are biochemically verified abstinence, length of abstinence, continuous abstinence, cigarettes per day, and quit attempts.

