### General analytic approach

We hypothesize that self-reported 7-day point prevalence abstinence rates will be greater in MAPS + than in ST. All data analyses will be performed using SAS version 9.4 with significance set at 0.05 for statistical tests of primary hypotheses. Descriptive statistics will be used for initial review of distributions and determination of needs for transformation prior to primary analyses. Group differences in baseline measures will be assessed and any variable that exhibits a group difference at p < .10 will be added as a covariate in the primary analyses.

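### A 30-day smoking criterion at entry and a 7-day abstinence outcome let some participants meet the primary outcome at baseline, and the models make no fixed provision for it

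*Protocol article*

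**What the plan says.** Under Recruitment and participants, the protocol article sets two smoking criteria: "≥ 100 lifetime cigarettes" and "self-report of smoking ≥ 1 cigarette in past 30 days". It sets no requirement for the past 7 days, for daily smoking or for a minimum number of cigarettes per day. The nearest exclusion covers people "currently receiving behavioral or pharmacological tobacco treatment". That removes people in treatment, but not unaided recent quitters or infrequent smokers.

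Under Smoking abstinence, the article states: "Our primary outcome is self-reported 7-day point prevalence abstinence at 24 months", and "participants who report no smoking in the previous 7 days are considered abstinent". The Study design overview words the time frame as the whole 24 months but uses the same 7-day definition.

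Nondaily smokers are expected, because randomisation is stratified on "daily vs. nondaily smoking" (Procedures). Table 1 schedules smoking status at baseline as well as at the monthly and follow-up assessments.

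On adjustment, the General analytic approach says that "any variable that exhibits a group difference at p < .10 will be added as a covariate in the primary analyses". The Analytic plan for primary outcome repeats that rule for the models. Apart from such covariates, it names only treatment group, time and their interaction.

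**The concern.** The entry window (30 days) is wider than the outcome window (7 days). Someone whose last cigarette was 8 to 30 days before screening passes the entry criterion and satisfies the abstinence definition on the same day. An occasional smoker whose habit never changes can also be scored abstinent at 24 months because of when the assessment falls.

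For these people, abstinence at 24 months does not show a move from smoking to not smoking, although the primary aim is framed as facilitating cessation. They can raise the abstinence rate in both arms. If treatment does less for them than for current smokers, they also shrink the difference and cost power.

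The stated covariate rule does not deal with this. It selects variables on chance imbalance between arms, not on how strongly they predict the outcome. Daily/nondaily status is balanced by stratification, so the rule is unlikely to pick it. Baseline 7-day status would enter only if the arms happened to differ on it. Smoking status at entry is plausibly among the strongest predictors of smoking status later, yet whether it enters the model is left to chance.

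**Working it through.** **Inputs from the article (Power and sample size).** 170 per group; 24-month abstinence 16% in ST and 29% in MAPS+; two-sided alpha 0.05; stated power at least 0.80 for the logistic regression at 24 months.

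**Step 1: the plan's own figure.** For two proportions with n per arm, difference Δ = p2 − p1 and mean rate p̄:

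power = Φ{ [Δ − 1.96·√(2p̄(1−p̄)/n)] / √([p1(1−p1) + p2(1−p2)]/n) }

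With p1 = 0.16, p2 = 0.29, p̄ = 0.225 and n = 170, the two standard errors are 0.0453 and 0.0447. Power = Φ[(0.13 − 1.96 × 0.0453)/0.0447] = Φ(0.92) = 0.82. A Wald test on the log odds ratio gives 0.81. The stated figure is reproduced.

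**Step 2: can a baseline-abstinent person be enrolled?** Take someone with 100 or more lifetime cigarettes, the last one 15 days ago, and no current treatment. Both smoking criteria are met and the treatment exclusion does not apply. The person has not smoked in the previous 7 days, so also meets the abstinence definition. No other criterion intervenes.

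**Step 3: illustration of the effect on power.** Let a share f of each arm be 7-day abstinent at baseline, with 24-month abstinence q_ST and q_MAPS+. Let 16% and 29% apply to everyone else. Then

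arm rate = (1 − f)·p + f·q.

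The article gives neither f nor q; all values of both are assumptions.

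| f | q, ST / MAPS+ | ST rate | MAPS+ rate | Difference (points) | Power |
|---|---|---|---|---|---|
| 0 | – | 16.0% | 29.0% | 13.0 | 0.82 |
| 5% | 0.40 / 0.40 | 17.2% | 29.55% | 12.35 | 0.77 |
| 5% | 0.60 / 0.60 | 18.2% | 30.55% | 12.35 | 0.76 |
| 10% | 0.40 / 0.40 | 18.4% | 30.1% | 11.7 | 0.71 |
| 10% | 0.60 / 0.60 | 20.4% | 32.1% | 11.7 | 0.69 |
| 5% | 0.40 / 0.53 | 17.2% | 30.2% | 13.0 | 0.81 |
| 10% | 0.40 / 0.53 | 18.4% | 31.4% | 13.0 | 0.79 |

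Rows 2 to 5 assume no treatment effect in these people. The last two rows give them the same 13-point effect as everyone else. At f = 2% with no effect and q from 0.3 to 0.7, power is 0.79–0.80.

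**Step 4: share of apparent successes.** With f = 10% and q = 0.5 in both arms, the ST rate is 0.9 × 0.16 + 0.1 × 0.5 = 0.194. Of that, 0.05/0.194 = 26% would be people who were already abstinent at entry.

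**Step 5: false-positive rate.** Under no treatment effect, both arms have the same mixed rate. Simulated two-sided type I error was 0.050, 0.051 and 0.050 at f = 0, 10% and 20%.

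**The case against.** The case on the other side has five parts.

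- **Treatment may help these people too.** MAPS+ aims at maintaining abstinence as well as starting it. Its text content is tailored to smoking status, and its counselling calls can be clustered when a participant is struggling to stay abstinent. Zero effect is therefore a pessimistic assumption, and with a 13-point effect the power loss nearly disappears. This stands, so the power figures are an illustration and not an estimate.
- **The planning rates may already include them.** The 16% and 29% are based on the team's earlier trial, whose entry rule the article does not give. If it was similar, the mixture in Step 3 counts these people twice. This stands. It cannot be said that the ST rate will exceed 16%.
- **There is no bias between arms.** This stands. A reader might infer that the mismatch favours MAPS+ or inflates the false-positive rate. Randomisation and Step 5 show otherwise.
- **Other outcomes help.** The article also evaluates 30-day abstinence, and nobody who meets the entry criterion can meet that outcome at the same moment. Continuous abstinence, length of abstinence, cigarettes per day and cotinine verification help to separate sustained quitting from a chance 7-day gap. This stands in part: it aids interpretation but does not change the primary analysis. The GEE analysis is also stated to have power of at least 0.95, and no loss was computed for it.
- **Adjustment belongs in an unseen analysis plan.** This carries less weight, because the article states a covariate rule, and that rule selects on imbalance. Baseline 7-day status could be selected by it, but only through chance.

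A reader might also infer that entry should be tightened to smoking in the past 7 days. The article does not compel that. Enrolling nondaily smokers is deliberate, and a change during ongoing recruitment would give two differently selected cohorts.

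**Conclusion.** The point holds as a limited one. The text allows people who already meet the 7-day definition to be randomised and later counted as abstinent, and the stated models do not routinely account for it. The consequences are possible inflation of abstinence in both arms, possible dilution of the difference, and a less clear reading of the result as cessation.

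The size cannot be established from the article. If these people are 5% to 10% of the sample and treatment does nothing for them, 24-month power is roughly 0.69–0.77 in place of 0.82. With a 13-point effect in them (40% versus 53%), it is 0.79–0.81. If the planning rates already include such people, the loss against plan is smaller still. The documents do not support a claim that the trial is underpowered for this reason, or that the outcome fails to measure cessation in the sample as a whole.

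The part that does not depend on these assumptions is the covariate rule. It leaves a plausibly strong predictor, already scheduled for collection, to enter the model only by accident of imbalance.

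**What to change.** In the General analytic approach and the Analytic plan for primary outcome:

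1. Name baseline 7-day smoking status and the daily/nondaily stratification factor as fixed covariates in the primary logistic and GEE models, whatever their balance between arms. For these two variables this replaces the p < .10 rule.
2. Pre-specify one sensitivity analysis of the primary outcome that excludes participants who were 7-day abstinent at baseline. The exclusion rests on a pre-randomisation characteristic, so the comparison between the remaining groups is still a randomised one.
3. Report the number of such participants by arm in the baseline table, so that readers can judge which part of the range above applies.

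No change to eligibility is proposed.

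The cost is two model terms and one extra analysis. No new data are needed, provided that the baseline smoking-status item in Table 1 records the past 7 days; the article does not spell out the item, so this should be confirmed. The sensitivity analysis uses fewer people. If 16% and 29% applied to those who remain, its power would be 0.80 with 5% excluded and 0.78 with 10% excluded, so it should be read as support for the primary result and not as a second test. The change should be recorded before outcome data are seen by arm.
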